## Abstract

**Background:**

Home ultraviolet B (UVB) treatment is a much-debated treatment, especially with regard to effectiveness, safety and side effects. However, it is increasingly being prescribed, especially in the Netherlands. Despite ongoing discussions, no randomised research has been performed, and only two studies actually compare two groups of patients. Thus, firm evidence to support or discourage the use of home UVB phototherapy has not yet been obtained. This is the goal of the present study, the PLUTO study (Dutch acronym for "national trial on home UVB phototherapy for psoriasis").

**Methods:**

We designed a pragmatic randomised single-blind multi-centre trial. This trial is designed to evaluate the impact of home UVB treatment versus UVB phototherapy in a hospital outpatient clinic as to effectiveness, quality of life and cost-effectiveness. In total 196 patients with psoriasis who were clinically eligible for UVB phototherapy were included. Normally 85% of the patients treated with UVB show a relevant clinical response. With a power of 80% and a 0.05 significance level it will be possible to detect a reduction in effectiveness of 15%. Effectiveness will be determined by calculating differences in the Psoriasis Area and Severity Index (PASI) and the Self Administered PASI (SAPASI) scores. Quality of life is measured using several validated generic questionnaires and a disease-specific questionnaire. Other outcome measures include costs, side effects, dosimetry, concomitant use of medication and patient satisfaction. Patients are followed throughout the therapy and for 12 months thereafter. The study is no longer recruiting patients, and is expected to report in 2006.

**Discussion:**

In the field of home UVB phototherapy this trial is the first randomised parallel group study. As such, this trial addresses the weaknesses encountered in previous studies. The pragmatic design ensures that the results can be well generalised to the target population. Because, in addition to effectiveness, aspects such as quality of life and cost-effectiveness are also taken into consideration, this study will produce valuable evidence to either support or discourage prescription of home UVB phototherapy.

**Trial registration:**

Current controlled trials/Nederlands Trial register: ISRCTN83025173. Clinicaltrials.gov: NCT00150930

## Background

About 2% to 4% of the Dutch population suffer from psoriasis. Psoriasis is a chronic recurrent skin disorder characterised by erythematosquamous lesions (plaques). Usually the affected areas are few, but occasionaly the disease is more generalised. Psoriasis can be treated topically by application of creams and ointments, for instance corticosteroids and vitamin D_3_. For most patients topical therapy will suffice. However, for some patients the area involved is so extensive that local treatment is not feasible. In other cases the skin lesions no longer respond to topical treatment. In that case the dermatologist may start irradiation with ultraviolet (UV) light or prescribe systemic medication. UV irradiation of the skin can be performed with different types of UV light: e.g. UVA, broadband UVB, or narrowband UVB. UVB irradiation is usually prescribed as a single therapy. However, adjuvant use of topical therapy may be continued.

UVB therapy has considerable consequences for the patient because it is nearly always carried out in a hospital outpatient clinic. The UVB irradiation itself normally takes only a few minutes, but to receive the irradiation patients have to travel to the outpatient department during working hours two to three times a week. In general it is a relatively time-consuming treatment. For hospital personnel as well, this mode of therapy demands a considerable investment of time. They have to determine the dosage, set the machine to the proper dosage, and fill out the medical records for each patient visit.

To overcome the drawbacks of UVB treatment in the outpatient clinic, home UVB phototherapy was introduced over 25 years ago [1-4]. Ever since, however, the safety and effectiveness of home UVB have been the subject of debate [5-13]. Despite all discussion, increasing numbers of dermatologists seem to be prescribing home UVB phototherapy to their patients.

In an earlier study we listed all known publications and studies on home UVB phototherapy, and conducted a survey among dermatologists [14]. We found that in the Netherlands home UVB is currently prescribed to approximately 5% of the UVB-treated patients, with some dermatologists prescribing it in 100% of the cases. We also demonstrated that there is no firm evidence that would either support or dissuade from prescribing home UVB phototherapy. Glaringly absent is any randomised research in this area. This lack of research has resulted in ongoing discussions and the dissemination of personal, non-evidence based opinions, especially with regard to issues like effectiveness, side effects and cost [14]. Thus, in general, home UVB phototherapy remains a debated treatment. We concluded that only randomised research on home UVB phototherapy as compared to UVB treatment in an outpatient setting could resolve the issue [14].

In this paper, we describe a randomised pragmatic trial that we are currently conducting, a national trial on home UVB phototherapy for psoriasis. The Dutch acronym for this trial is PLUTO (Psoriasis: Landelijk UVB Thuisbelichtings Onderzoek). The trial is designed to evaluate the impact of home UVB phototherapy versus conventional outpatient UVB phototherapy on effectiveness, quality of life and cost-effectiveness. The focus is on narrowband UVB treatment (TL-01 lamps). The study tests the hypothesis that home UVB phototherapy is as effective as outpatient UVB phototherapy. We further expect a better quality of life when patients are treated at home, and we hypothesize that home treatment will have similar or reduced total costs. This article presents the design of this trial.

## Methods

### Objective

The aim of this study is to compare home UVB (TL-01) phototherapy with the current outpatient UVB (TL-01) phototherapy for patients with psoriasis. This objective was specified by the following research questions. Compared to outpatient UVB phototherapy:

1. Is home UVB phototherapy for patients with psoriasis equally effective?

2. Does home UVB phototherapy yield a better quality of life?

3. Are costs for home UVB phototherapy higher, lower or similar?

4. Is home UVB phototherapy cost-effective?

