### Sample size

The sample size could not be calculated on the basis of presumed differences in effectiveness as there is no clear data available on the possible differences in treatment effects. However, based on the data available from a 1993 pilot study [16] and recent experience with home UVB phototherapy, we in fact expected the effectiveness of both therapies to be similar. The sample size was therefore calculated in accordance with a negative trial approach [17]. We considered a 50% or greater improvement in the psoriasis severity from baseline to be a relevant clinical response. A systematic review by Spuls et al. indicates that approximately 85% of the patients treated with UVB show at least a 50% improvement in their psoriasis [18]. Thus, with N = 90 per per treatment group and at α = 0.05 and β = 0.20 (power 80%), we would be able to show a difference in effectiveness of 15% or more; i.e., a reduction in effectiveness from 85% to 70% or less should be distinguishable. To allow for missing data and losses to follow-up (i.e. withdrawals, incomplete case register forms) we aimed at 100 patients per group, 200 in total. To obtain accurate estimates of the cumulative costs of UVB treatment a consecutive sample of 100 patients (50 per group) was considered to be sufficient, because little variation was expected in treatment duration, number of UVB irradiations, and use of concomitant medication.

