#### Cost-effectiveness

A direct comparison will be made between the effectiveness of the two therapeutic modalities and their associated cost. Incremental cost per additional patient treated successfully and costs per QALY gained will be estimated. Cost-effectiveness (CE) will be calculated for a time horizon of 12 (11–13) months after randomisation/inclusion. The quality of life (QoL) questionnaires were no longer administered after cessation of irradiation. Based on the association between clinical symptoms and QoL, the impact in terms of QoL for the remaining follow-up, i.e. up to 12 months, will be extrapolated using regression models. Subsequently, cost per QALY can be calculated. In case the difference in effectiveness is less than 15%, we will consider this as equal effectiveness and will limit the economic evaluation to a cost minimisation analysis.

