### Statistical analysis

All data will be analysed according to the intention to treat principle, meaning all included patients will be analysed according to the group they were randomised to. This includes patients who dropped out or changed therapy. The statistical methods that will be used are chosen in accordance with the type of data that is available. For continuous data differences and their 95% Confidence Intervals (95% CIs) will be presented. In case of binary outcomes, differences in proportion with 95% CIs will be calculated. Whether randomisation was successful will be determined by assessing comparability of baseline characteristics. No formal statistical tests are foreseen. In the event apparent differences are noted, a multivariate analysis will be performed to adjust for potential confounding.

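### Research question 1 and the equal-effectiveness rule have no direction, but the sample size covers only a 15-point loss; the 80% power holds for that loss and does not carry over to equality

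*Protocol article*

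**What the plan says.** The Objective section of the protocol article puts research question 1 as "Is home UVB phototherapy for patients with psoriasis equally effective". The Background section gives the hypothesis: "The study tests the hypothesis that home UVB phototherapy is as effective as outpatient UVB phototherapy".

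The Sample size section expects similar results in both arms and says "The sample size was therefore calculated in accordance with a negative trial approach". Its inputs are a response rate from a systematic review ("approximately 85% of the patients treated with UVB show at least a 50% improvement in their psoriasis") and the design values "with N = 90 per per treatment group and at α = 0.05 and β = 0.20 (power 80"%). The conclusion is one-directional: "a reduction in effectiveness from 85% to 70% or less should be distinguishable". The Abstract and the Discussion also describe the detectable difference as a reduction. Whether α is one- or two-sided is not stated.

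Under Outcome assessment, Cost-effectiveness, the article adds a decision rule: "In case the difference in effectiveness is less than 15%, we will consider this as equal effectiveness". In that case the economic evaluation is limited to cost minimisation. The rule names no direction and no confidence limit. For analysis, "In case of binary outcomes, differences in proportion with 95% CIs will be calculated".

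**The concern.** The article asks one question and sizes the trial for another. Equality, or a difference of less than 15% with no sign attached, is a two-sided statement. Excluding a fall from 85% to 70% is a one-sided one. Power for the second is not power for the first.

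Two things are at stake. First, a reader may take the 80% as support for a finding of equal effectiveness, which it is not. Second, the equality rule decides the form of the economic evaluation (research questions 3 and 4). As worded it can be met by a point estimate alone, whichever way the difference runs and however wide its interval. It could therefore pass the very loss the trial was sized to exclude, or set aside a real home advantage.

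**Working it through.** **Inputs.** Response 85% in both arms (the review figure and the expectation of similarity, Sample size); margin 15 points; 90 per group planned; 98 per group randomised (Table 3: 50 + 48 in each arm); 95% CIs (Statistical analysis). d is home minus outpatient.

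**1. Reproducing the 90 per group and 80%.** To exclude a 15-point loss when the true rates are equal:

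n = 2 × 0.85 × 0.15 × (z_α + z_β)² / 0.15²

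- One-sided 0.025 (lower limit of a two-sided 95% CI): 0.255 × (1.960 + 0.842)² / 0.0225 = 88.95, so 89 per group.
- One-sided 0.05: 70.1, so 71 per group.

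For comparison, a conventional test of 85% v 70% needs 121 per group two-sided (67.6% power at 90), or 95 one-sided at 5% (78.2% power at 90).

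The closest match to 90 is the lower 95% limit. With SE = √(0.255/n):

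- n = 90: SE = 0.0532; power = Φ(0.15/0.0532 − 1.96) = 80.5%.
- n = 98: SE = 0.0510; power = Φ(0.15/0.0510 − 1.96) = 83.7%, about 84%.

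**2. Power if equality is meant in both directions.** Require the whole CI to lie inside ±15 points. With true rates equal, power = 2 × Φ(0.15/SE − z) − 1.

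| Per group | 95% CI | 90% CI (two one-sided 5% tests) |
|---|---|---|
| 90 | 60.9% | 75.9% |
| 98 | 67.3% | 80.5% |

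Exact binomial enumeration gives 60.8% and 76.2% at 90, and 67.1% and 81.1% at 98. For 80% power the trial would need 119.1, so 120 per group (95% CI), or 97.1, so 98 per group (90% CI).

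**3. The economic rule read literally (|d| below 15 points, point estimate only, 98 per group).**

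- True 70% home v 85% outpatient: SE = √((0.70 × 0.30 + 0.85 × 0.15)/98) = 0.0587. P(equal) ≈ Φ(0.30/0.0587) − Φ(0) = 50%; the exact binomial figure is about 49%. Requiring the lower 95% limit to be above −15 points cuts this to about 2.6%.
- True 94% home v 85% outpatient: SE = √((0.94 × 0.06 + 0.85 × 0.15)/98) = 0.0433. P(equal) ≈ Φ(0.06/0.0433) − Φ(−0.24/0.0433) = 92%; exact, about 91%.
- If exactly 94% v 85% were observed, d = +9 points with 95% CI 9 ± 1.96 × 4.33, or 0.5 to 17.5. The interval excludes zero, yet the rule returns equal effectiveness.

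**The case against.** The strongest reply is that the stated power is not wrong. The Abstract, Sample size and Discussion all tie it to a reduction, and it reproduces. A reader might infer that the true power is 61% and not 80%. The article does not support that. It nowhere claims 80% power for equality, and 61% requires a rule it never states: a symmetric margin, the whole 95% CI inside it, and 90 per group. This part of the reply stands.

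The upper bound also has little substance. With 85% response in outpatients, +15 points means 100% response at home, and the hypothesis that home is as effective can be read as no worse. This stands too. It argues for restating the question in one direction and not for enlarging the trial.

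It can further be said that the cited sample size method is not shown, and that sidedness is a detail a condensed article may leave to the full protocol. That is fair: the one-sided 0.025 reading is inferred from the arithmetic. But the wording of question 1 and of the equality rule is fixed in this text.

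Finally, the rule governs only the form of the economic evaluation. Effectiveness is still reported with its 95% CI, and the Statistical analysis section, under Cost-effectiveness, says without any stated condition that the incremental cost per successfully treated patient will first be estimated, with bootstrapping. So a home benefit would not vanish from the report. However, that unconditional plan and the restriction to cost minimisation then have to be reconciled.

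**Conclusion.** The mismatch is real but is mainly one of wording. The sample size and its 80% stand for the one-directional claim. They do not carry over to two-sided equality, where CI-based power runs from 61% to 76% at 90 per group and from 67% to 80% at 98. These figures assume 85% response in both arms, a ±15-point margin and complete outcome data.

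The economic rule is the more consequential part. Taken literally, it calls a true 15-point loss equal about half the time, although excluding that loss is what the trial was sized for. It calls a true 9-point home advantage equal about nine times in ten. These two figures assume that the rule is applied to the point estimate, as its wording implies, with all 98 per group analysed.

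**What to change.** 1. State research question 1 and the Background hypothesis as: home UVB is no more than 15 points less effective than outpatient UVB. Judge this by the lower limit of the two-sided 95% CI for home minus outpatient (one-sided α 0.025), and say that the 80% power refers to this claim.

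2. Replace the point-estimate rule under Outcome assessment, Cost-effectiveness, by one of these:
   - always run the cost-effectiveness analysis with bootstrapped joint costs and effects already described under Statistical analysis; or
   - limit the evaluation to cost minimisation only when the whole 95% CI lies within ±15 points and does not exclude zero.

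Merely giving the rule the one-sided direction of item 1 would not do: every home advantage, however large, would then go to cost minimisation.

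The first option is the cleaner one. Under the second, a true 94% v 85% advantage could still lead to cost minimisation. The upper limit is below 15 when d < 0.15 − 1.96 × 0.0433 = 0.065, which has probability Φ((0.065 − 0.09)/0.0433), about 28%, against 91% now.

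No extra patients are needed. The cost is a weaker claim (not relevantly worse, instead of equally effective) and less frequent cost minimisation: with truly equal rates and 98 per group, the second option would allow it about 67% of the time, against over 99% under the present rule.

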### Design

We conducted a pragmatic randomised parallel group single-blind multi-centre trial among psoriasis patients eligible for narrowband UVB (TL-01) phototherapy. Patients were randomly allocated to two groups, thus obtaining two treatment groups of equivalent prognosis. One group was given home UVB phototherapy and the other UVB phototherapy in the outpatient department of the participating hospitals.

The design was chosen to be 'pragmatic' in order to compare the two treatments under the conditions in which they would be applied in daily practice [15]. Accordingly, in our pragmatic trial we randomised the patients into two treatment groups, but we did not impose a prespecified treatment regimen on the participants. Instead, we urged dermatologists to carry out the assigned UVB treatments as they would normally, and thus to act in accordance with their own views. Consequently, all of the implicit differences in the two treatments were compared, including factors such as frequency of irradiations, dosage, compliance, concomitant medication, support and equipment. We did not control for these and other possible differences relating to the treatment, because they cannot be controlled for in a real life situation.

The locations of the two treatments (at home versus in the outpatient department) of course made blinding of the participants impossible. Because of the pragmatic design of the study it was not desirable to blind the dermatologist. However, we arranged for the extent and severity of the psoriasis to be assessed by an independant research nurse blinded to treatment form.

### Study population

Psoriasis patients who were clinically eligible for narrowband UVB (TL-01) phototherapy ànd who had had this therapy prescribed by their own dermatologist were invited to participate in the study. All inclusion and exclusion criteria are displayed in table 1.

**Table 1 T1:** Eligibility criteria. Study participants were subject to the following inclusion and exclusion criteria.

**Inclusion criteria**:
1. Guttate or plaque psoriasis, clinically eligible for narrowband UVB (TL-01) phototherapy;
2. Willing to undergo treatment according to randomisation.

**Exclusion criteria**:

1. No informed consent:
• age below 18 years;
• not willing to accept one of the two treatments offered;
2. Practical reasons:
• not able to receive one of the two treatments offered (e.g. lack of space at home/living too far from hospital etc.);
• analphabetism (unable to read the patient information and the questionnaires, unable to provide written answers and written informed consent);
• lack of command of the Dutch language;
• not in possession of a telephone.
3. Expected non-compliance:
lack of understanding of what the study/treatment is about, and its potential consequences.
4. Medical contraindications:
• Malignancy of the skin in the past/at present;
• known UVB-allergy or chronic polymorphic photodermatosis;
• use (at time of inclusion) of medication with known phototoxic or photoallergic properties;
• use (at time of inclusion) of systemic antipsoriatic medication (cyclosporin, methotrexate, neotigason, fumaric acid);
• history of exposure to ionising radiation.

The main selection criterion of being "clinically eligible for narrowband UVB treatment" was purely pragmatic and was left to the discretion of the participating dermatologist. However, dermatologists were explicitly discouraged from increasing the number of their prescriptions on behalf of the study. No financial benefit or other compensation was offered to participating dermatologists for their efforts; this to avoid any conflict of interest and to include only those patients who would otherwise have received narrowband UVB treatment. Likewise, the patients also received no material compensation for their participation in the study.

### Sample size

The sample size could not be calculated on the basis of presumed differences in effectiveness as there is no clear data available on the possible differences in treatment effects. However, based on the data available from a 1993 pilot study [16] and recent experience with home UVB phototherapy, we in fact expected the effectiveness of both therapies to be similar. The sample size was therefore calculated in accordance with a negative trial approach [17]. We considered a 50% or greater improvement in the psoriasis severity from baseline to be a relevant clinical response. A systematic review by Spuls et al. indicates that approximately 85% of the patients treated with UVB show at least a 50% improvement in their psoriasis [18]. Thus, with N = 90 per per treatment group and at α = 0.05 and β = 0.20 (power 80%), we would be able to show a difference in effectiveness of 15% or more; i.e., a reduction in effectiveness from 85% to 70% or less should be distinguishable. To allow for missing data and losses to follow-up (i.e. withdrawals, incomplete case register forms) we aimed at 100 patients per group, 200 in total. To obtain accurate estimates of the cumulative costs of UVB treatment a consecutive sample of 100 patients (50 per group) was considered to be sufficient, because little variation was expected in treatment duration, number of UVB irradiations, and use of concomitant medication.

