Overall, we feel that this trial has many benefits and will prove to be a very valuable addition to the current literature in the field. It is the first trial to compare these two commonly used treatments directly in a randomised parallel group design. Moreover, the study design allows for more than one objective. Besides clinical effectiveness, it also evaluates quality of life and cost-effectiveness. Being a pragmatic trial, it will be easy to generalise the results of this study to the target population. With 196 participants, the study is adequately powered to detect a 15% reduction in effectiveness, and the other outcome parameters can also be determined adequately. The results of this study will be available in 2006.

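### The 80% power at 90 per group is power to exclude a 15-point loss when both therapies respond at 85%, but the Abstract and Sample size section describe it as power to detect a true fall from 85% to 70%

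*Protocol article*

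**What the plan says.** The Sample size section of the Methods gives the reasoning in three steps.

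- Expectation and approach: "we in fact expected the effectiveness of both therapies to be similar", and "The sample size was therefore calculated in accordance with a negative trial approach".
- Inputs: a response is an improvement of at least 50% from baseline, and a systematic review is cited for "approximately 85% of the patients treated with UVB show at least a 50% improvement in their psoriasis". The figures are 90 per group, α = 0.05 and β = 0.20. Whether α is one- or two-sided is not stated.
- Interpretation: with these figures the trial is said to be able to show a difference of 15% or more, so that "a reduction in effectiveness from 85% to 70% or less should be distinguishable".

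The Abstract (Methods) carries only the interpretation: "With a power of 80% and a 0.05 significance level it will be possible to detect a reduction in effectiveness of 15" per cent. The Discussion says: "With 196 participants, the study is adequately powered to detect a 15% reduction in effectiveness". It gives neither an α nor a power figure.

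Two other places bear on the reading. The Statistical analysis section plans interval estimates: "In case of binary outcomes, differences in proportion with 95% CIs will be calculated". The Cost-effectiveness section of the Methods treats a difference below 15% as equal effectiveness.

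**The concern.** Two different questions share the figure of 15 percentage points. One is whether the trial can rule out a loss that large when the therapies are in fact equal. The other is whether it can show a difference when home treatment really is that much worse. At a given sample size these have different power, because the assumed truth and the value to be excluded both change.

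The approach named in the Sample size section belongs to the first question. The sentence that interprets it, and the Abstract, state the second. A reader of the Abstract sees no mention of the negative trial approach. That reader could take a non-significant difference as reassurance backed by 80% power against a 15-point loss. The useful property of the design, that its confidence interval can exclude such a loss, is implied by the approach but never put in a sentence.

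**Working it through.** **Inputs.** Response rate 85%, difference or margin 15 points, 90 per group, α = 0.05 and power 80% are from the Sample size section. Enrolment of 196, or 98 per group, is from the Results. Two-sided α is an inference from α = 0.05 together with the 95% CIs in the Statistical analysis section. Normal quantiles: 1.960 (two-sided 0.05), 1.645 (one-sided 0.05), 0.8416 (80% power).

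**1. Reproduce the plan's figure: exclude a 15-point loss, both arms at 85%.**

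n = (1.960 + 0.8416)² × 2 × 0.85 × 0.15 / 0.15² = 7.849 × 0.255 / 0.0225 = 88.95, so 89 per group.

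Power at 90: SE = √(0.255/90) = 0.0532; 0.15/0.0532 − 1.960 = 0.858; Φ(0.858) = 80.5% (80.4% by exact enumeration).

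The stated 90 per group and 80% power reproduce.

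**2. Power to detect 85% v 70%, two-sided 0.05, at 90 per group.**

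- Unpooled SE = √[(0.85 × 0.15 + 0.70 × 0.30)/90] = √(0.3375/90) = 0.0612. Then 0.15/0.0612 − 1.960 = 0.489, and power is 68.8%.
- Pooled SE under no difference = √(2 × 0.775 × 0.225/90) = 0.0622. Then (0.15 − 1.960 × 0.0622)/0.0612 = 0.457, and power is 67.6%.
- Exact enumeration: 67.9% (pooled) and 69.3% (unpooled).

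The stated 80% does not reproduce on this reading. To reach it would take 118 (unpooled) to 121 (pooled) per group:

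- unpooled: 7.849 × 0.3375 / 0.0225 = 117.7;
- pooled: (1.960 × √0.34875 + 0.8416 × √0.3375)² / 0.0225 = 120.5.

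**3. The same question at one-sided 0.05.** At 90 per group, power is 78.2% (pooled) or 78.9% (unpooled), and 80% needs 95 or 93 per group. This is close to 80%, but 90 is not the number the calculation gives.

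**4. All 196 patients, 98 per group, assuming every outcome is observed.**

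| Question | 90 per group | 98 per group |
|---|---|---|
| Exclude a 15-point loss, both 85%, two-sided 95% CI | 80% | 84% |
| Detect 85% v 70%, two-sided 0.05 | 68–69% | 71–73% |
| Detect 85% v 70%, one-sided 0.05 | 78–79% | 81–82% |

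**The case against.** **The sample size is correct for the approach named.** This stands. A reader might infer from the 68% that the trial was miscalculated or should have had about 120 per group. The document does not support that: it says that similarity was expected and that the size was calculated for that reason by a negative trial approach, and on that approach 90 is right. The larger number would be needed only if two-sided detection of a difference were the aim. The section, however, goes on to explain its 80% as the ability to show a difference, with both rates named, so naming the approach does not correct that explanation.

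**Sidedness is not stated, and the wording is directional.** This stands in part. At one-sided 0.05 the shortfall at 90 per group is only 1–2 points. At 98 per group power is 81–82%, so the Discussion sentence, which gives no α or power and refers to all 196 participants, is not clearly wrong. Against this, no one-sided test is planned in the article, and the planned 95% CIs are two-sided by convention.

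**The harm presumes a test against zero.** This also stands in part. A reader might turn 68% power into about a 3-in-10 chance of wrongly declaring the therapies equal. That does not follow: about 3 in 10 is the chance that the interval fails to exclude zero. If the interval is judged against 15 points, a true fall to 70% would be accepted as excluded in only about 2.6% of trials (exact enumeration, 90 or 98 per group).

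**The intended property is partly visible.** The approach, the hypothesis that home treatment is as effective, and the 15% limit in the Cost-effectiveness section are all given. What is lacking is the sentence that joins them.

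**Conclusion.** The defect is in the description of the power, not in the number of patients. At 90 per group the design has 80% power for a two-sided 95% CI to exclude a 15-point loss if both response rates are 85%. The Sample size section and the Abstract attach that 80% to detecting a true fall from 85% to 70%, for which power is about 68–69%, some 11–12 points lower.

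The size of the gap rests on a two-sided α, which is inferred. At one-sided 0.05 it shrinks to 1–2 points at 90 per group. The Discussion sentence should be aligned with the others rather than counted as a separate error. Figures for 98 per group are upper values: the Sample size section itself allows for missing data and losses, and the Results report seven patients who never started therapy.

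**What to change.** Reword the power statement in the Abstract (Methods) and in the Sample size section, for example:

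> With 90 evaluable patients per group there is 80% power for the two-sided 95% CI to exclude a reduction of 15 percentage points or more if both response rates are 85%. Power to detect a true fall from 85% to 70% (two-sided 0.05) is about 68%.

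This states the margin and the sidedness along with the power. If a one-sided α was in fact used, the article should say so and give the matching figures.

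Align the Discussion sentence. If it keeps the reference to 196 participants, give about 84% (exclusion) and about 72% (detection, two-sided) for 98 per group, as upper figures that assume complete outcome data.

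The cost is text only. The number of patients, the 15-point limit and the planned interval analysis are unchanged; the stated detection power becomes less favourable.
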